#### Outcome measures and assessments

For the effectiveness trial, change in PTSD symptoms is the primary outcome measure (**Table 4**). Changes in depressive, pain, anxiety symptoms and quality of life are exploratory outcome measures.

**Table 4 pone.0275774.t004:** Primary and exploratory outcome measures for the effectiveness evaluation.

Outcome Measure	Explanation
Change in PTSD symptoms *Primary*: Change in PCL-5 scores from baseline to post-treatment (6-weeks).	The PCL-5 is a well-validated, widely used, and easy to administer 20-item self-report scale that is widely used in PTSD research and clinical practice [47]. Responses to each item relate to the four symptom clusters for PTSD, for which separate scores can be measured and used for additional analyses. The PCL-5 will be used for follow-up assessments over the CAPS-5 because of the feasibility of a self-report measure over a semi-structured interview and to reduce the reporting burden on participants.
*Exploratory*: Prolonged changes in PCL-5 scores from baseline to 12-week follow-up and 30-week follow-up.	
Change in depressive symptoms *Exploratory*: Change in depressive symptoms as measured by the nine-item Patient Health Questionnaire (PHQ-9) scores from baseline to 6-weeks, 12-weeks, and 30-weeks follow-ups.	PHQ-9 is a well-validated and widely used self-report scale used in depression research. Each item is rated on a 4-point scale for how much it bothered the participant in the past 2 weeks. A self-report scale is more feasible than an assessor-rated scale (e.g. HAM-D17) given the virtual nature of this study.
Change in pain symptoms *Exploratory*: Change in pain symptoms as measured by the Brief Pain Inventory (BPI) from baseline to 6-weeks, 12-weeks, and 30-weeks follow-ups.	BPI is a validated self-report scale used in pain trials and clinical pain practice and is a core outcome measure per the Initiative on Methods, Measurement, and Pain Assessment in Clinical Trials (IMMPACT) recommendations [50]. Two independent and clinically relevant measures are included: pain severity and pain interference with function.
Change in anxiety symptoms *Exploratory*: Change in anxiety symptoms as measured by the seven-item Generalized Anxiety Disorder scale (GAD-7) from baseline to 6-weeks, 12-weeks, and 30-weeks follow-ups.	GAD-7 is a validated and efficient tool that is used to screen and assess the severity of generalized anxiety disorder GAD clinically and in research. Each of the 7-items are rated on a 4-point scale for how often it bothered the participant in the past two weeks.
Change in Quality of Life *Exploratory*: Change in quality of life as measured by the 36-item Health-Related Quality of Life measurement (SF-36) from baseline to 6-weeks, 12-weeks, and 30-weeks follow-ups.	Change in health-related quality of life (SF-36) has been validated as quality of life measurement and is recommended by IMMPACT [50]. This measure is well-aligned to the intervention which may also improve overall quality of life (QoL) in addition to specific PTSD symptom improvement.

In addition to these primary and exploratory outcome measures, participants will also complete an intake survey for their baseline assessment. This survey will collect demographic information on age, partial date of birth (DOB), gender, race, ethnicity, employment status, military and/or RCMP service status, housing type, highest level of education achieved, smoking, caffeine intake, drug and alcohol use, duration of PTSD diagnosis, and past treatment history for their PTSD. Participants will also be asked about their psychiatric history including age of first contact with services for mental illness (and which illness(es)), history of hospital admissions, and health service use. We will also collect data on medications used by participants including names, dosages (per day, total daily), and the reason for their use. This will include vitamins/minerals/herbal preparations and other over-the-counter (OTC) medications. Participants will not be excluded from the study for medication changes. Any changes to medications will be captured at follow-up assessments.

At the follow-up assessment timepoints, the following questionnaires will be administered: PCL-5, PHQ-9, BPI, GAD-7, SF-36. In addition, a post-intervention questionnaire will be administered after the v-SKY intervention. This will be at the T2 assessment for the active intervention group and the T3 assessment for the WLC group. This questionnaire will collect information on barriers and facilitators for the v-SKY intervention, the intervention’s instruction and setting, and level of satisfaction with the intervention. A flowchart of the study design is shown in **Fig 1**.

### Implementation evaluation design

The implementation evaluation will be conducted in parallel to the effectiveness trial based on the experiences and perspectives of RCT participants, v-SKY instructors, as well as health professionals and administrators that work with veterans. For RCT participants, this implementation evaluation will be conducted with participants who pass the T3 assessment timepoint. For health professionals and administrators and instructors, the evaluation will be conducted at the end of the effectiveness trial.

#### RE-AIM framework

The five dimensions of the RE-AIM framework will be explored amongst Canadian veterans with PTSD, v-SKY instructors, health professionals, and administrators that work with Canadian veterans (**Table 5**). We are focusing on adoption from the perspective of Canadian veterans and the people who work with Canadian veterans for this study because v-SKY is in the early stages of its implementation.

**Table 5 pone.0275774.t005:** Descriptions of the methodological approaches used to assess each RE-AIM dimension in each population.

RE-AIM dimension	Veterans	SKY Instructors	Health professionals and administrators
**Reach**	*Quantitative approach*: Measuring recruitment metrics, attrition, and demographics using detailed tracking logs and questionnaires. Comparison of baseline demographics to observational studies of Canadian veterans with PTSD [5–7] to determine representativeness.	Not assessed amongst instructors.	*Qualitative approach*: Assessing interest in the research study and for one-on-one semi-structured interviews.
**Effectiveness**	*Mixed-methods approach*: Measuring effects of intervention on health-related outcomes using validated questionnaires and assessing indicators of effectiveness through semi-structured interviews.	*Qualitative approach*: Assessing indicators of the v-SKY intervention’s effectiveness through semi-structured interviews.	*Qualitative approach*: Assessing indicators of the v-SKY intervention’s effectiveness through semi-structured interviews.
**Adoption**	*Mixed-methods approach*: Measuring the frequency of which SKY techniques are used and the factors that contribute to continued use of this practice using the combination of a post-intervention questionnaire and semi-structured interviews.	*Qualitative approach*: Assessing factors that may contribute to adoption of SKY techniques by participants through semi-structured interviews.	*Qualitative approach*: Assessing factors that contribute to adoption of the v-SKY intervention through semi-structured interviews.
**Implementation**	*Qualitative approach*: Assessing barriers and facilitators to implementation of the v-SKY intervention using the combination of a post-intervention questionnaire and semi-structured interviews.	*Mixed-methods approach*: Assessing barriers and facilitators to implementation of the v-SKY intervention through semi-structured interviews and cohort completion questionnaires.	Not assessed amongst health professionals and administrators.
**Maintenance**	*Qualitative approach*: Assessing whether or not participants are continuing to practice SKY and what factors contribute to this continued use through semi-structured interviews.	Not assessed amongst instructors.	Not assessed amongst health professionals and administrators.

#### Conceptual framework for implementation evaluation

While RE-AIM is used as the conceptual framework for studying effectiveness and implementation in this hybrid type II study, we will also employ Normalization Process Theory (NPT) as a means to understand adoption within the RE-AIM framework. NPT aims to estimate how likely an intervention may be incorporated into routine practice by highlighting the various facilitators and barriers in the early stages of its implementation [51]. NPT helps delineate how stakeholders make sense of an intervention, the cognitive and relational work required to participate, the collective actions required to make the intervention work and how to appraise outcomes and ongoing use (**Table 6**). NPT has been used elsewhere to evaluate implementation of mind-body interventions for individuals with multiple sclerosis [52].

**Table 6 pone.0275774.t006:** A Description of each core construct of Normalization Process Theory.

NPT Construct	Description
Coherence	Sense-making work for operationalizing a new program.
Cognitive Participation	Relational work done to sustain a community of practice around a new program.
Reflexive Monitoring	An ongoing assessment/appraisal of how new programs affect various stakeholders and the individuals around them.
Collective Action	The operational work conducted by stakeholders in order to enact a new program.

To integrate and implement the v-SKY intervention for Canadian veterans with PTSD, it is necessary to consider how the intervention is likely to be understood by the relevant stakeholders. Firstly, the SKY intervention is relatively new to Canadian veterans and the organizations and clinics that work with them. Although the intervention has been studied in other veteran populations, it is important to understand implementation in the Canadian context. Secondly, this is the first study focusing on the virtual implementation of the SKY intervention. It is important to study how virtual programming fits within the current treatment environment.

NPT has four main constructs that represent the different types of work that people do when faced with a new intervention such as v-SKY (**Table 6**). Adoption will be evaluated using each of these four constructs, which will be explored through one-on-one semi-structured interviews with RCT participants, SKY instructors, health professionals, and administrators that work with Canadian veterans.

#### Study population

The study populations for the implementation evaluation will consist of the veteran RCT participants recruited from across Canada, SKY instructors from the International Association for Human Values and Art of Living Foundation, and health professionals and administrators that work with veterans.

#### Participant recruitment and consent

*RCT participants*. Up to 16 RCT participants will be recruited for one-on-one semi-structured interviews. Participants who completed the v-SKY intervention and those who did not complete or dropped out of the intervention will be identified using criterion sampling. This will ensure that the perspectives of people who did not participate in the full trial will be assessed. Both completers and non-completers will be recruited for these interviews. Participants will begin to be identified for interviews after the T3 assessment timepoint, which is when the completion or non-completion status will be known. For these interviews, we aim to include French-speaking participants proportionate to the overall trial recruitment. An interview guide is located in **Section 4a of the S1 Appendix.**

*SKY instructors*. The SKY instructors from the International Association for Human Values and Art of Living Foundation that led v-SKY sessions throughout this study will be identified for one-on-one semi-structured interviews to discuss the virtual implementation of the v-SKY intervention. Informed consent will be obtained by research staff prior to any formal assessments. Convenience sampling will be used to recruit up to 8 interested instructors for these interviews. These instructors will provide further information about the virtual implementation of the v-SKY intervention by reflecting on their experiences in the trial. Recruitment of instructors will take place after the last cohort in the RCT trial is complete. An interview guide is located in **Section 4b of the S1 Appendix.**

Instructors will also complete a questionnaire after the completion of each cohort. The cohort completion questionnaire will allow instructors to document any relevant changes or deviations to the protocol within a cohort. This data will be used to understand the virtual implementation of SKY.

*Health professionals and administrators*. Health professionals and administrators that work with veterans will be identified by the study staff, investigators, and/or collaborators over the course of the study. Informed consent will be obtained by research staff prior to any formal assessments. Participants will include clinicians, clinic staff, and policy makers in relevant organizations pertaining to the care of people with PTSD. Stratified purposeful sampling will be used to identify candidates who are interested and able to participate in one-on-one interviews. Up to 16 stakeholders in leadership positions at OSI clinics and organizations that work with Canadian veterans will be recruited. Half of the participants will consist of clinicians who work with veterans, while the other half will consist of managers and personnel in leadership positions at clinics and organizations that work with veterans. Clinicians will be selected for their perspectives on implementation of the v-SKY intervention using their clinical expertise. Those in management positions will be selected for their perspectives on adoption of the v-SKY intervention using their knowledge of organizational and structural barriers. Recruitment of stakeholder participants will take place after the last cohort in the RCT trial is complete. For these interviews, we aim to include French-speaking personnel proportionate to the overall trial recruitment. An interview guide is located in **Section 4c of the S1 Appendix.**

We expect to identify emerging themes within the first six interviews with RCT participants, SKY instructors, and health professionals and administrators [53, 54]. Interviews will continue until data saturation occurs [53].

### Data management and confidentiality

All questionnaires and forms will be completed digitally using surveys hosted through Qualtrics and stored on a secure server based at Sinai Health System. All data will be coded with unique participant IDs to protect patient confidentiality and documents linking participants to their IDs will be stored on a secure database at Sinai Health System and maintained by the research staff for the duration of the study. The code key with identifying data will be stored on a secure server and will only be accessible to the research staff for the duration of the study, unless extenuating circumstances where a participant’s health is at risk and requires unblinding. The research team at Sinai Health System will also be in charge of maintaining the trial protocol and updating it with any amendments as approved by the relevant research ethics boards. They will update participants with any relevant modifications to the protocol and update the trial registry at clinicaltrials.gov accordingly.

RCT participants will be offered the v-SKY intervention at no financial cost. Participants are not expected to incur any additional financial costs to participate in this intervention and the associated assessments. RCT participants that complete all their assessments (up to and including the T4 assessment) will be entered into a draw for gift cards ($25 value). Participants will have a 10% chance of receiving a gift card for completing all study assessments. Any identifying information that is required for sending gift cards or conducting the draw will be stored separately from study information to prevent reidentification of the participant.

Participants will be informed that their participation in this study is voluntary. They may decide not to be in this study, or to be in the study now and then change their mind later. Leaving the study at any time will not affect their care at the partnering clinics and organizations. Participants may also refuse to answer any question they do not want to answer, or not answer an interview question by saying “pass”. If participants withdraw from the study early, any information that was collected will still be used for the study unless they request otherwise. No new information will be collected from them.

### Risks and safety

Previous investigations of SKY have found that SKY is well tolerated among participants with no reported adverse events [29, 55, 56]. Some theoretical adverse effects that could be experienced with SKY are mild anxiety, mild boredom, or mild detachment from one’s surroundings. Participants experiencing any new adverse effects will be advised to consult with their primary care provider. Instructors will be able to connect with study physicians if there are any acute medical issues during the v-SKY intervention. Instructors will consult with study staff to determine if participants experiencing such adverse effects should be permitted to continue. If considered medically unsafe to continue, the participant will be removed from the study and will be advised to consult with their primary health care provider or local emergency department. Participants will be assessed for suicidal ideation during each assessment (positive response to PHQ-9 question 9 ≥1). Any indication of a change in the participant’s overall mental health or risk of suicide will be reported immediately to study physicians for appropriate management. The questionnaires used in the study carry little risk, but participants may feel uncomfortable, sad, embarrassed, or anxious as some of the questions involve thinking about past trauma. Participants may refuse to answer questions or stop the interview at any time if there is any discomfort. There are no known nor expected risks for instructors, health professionals, and administrators that work with veterans.

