**Fig 1 pone.0275774.g001:**
[figure not shown]
Flowchart showing the timeline of the randomized controlled trial.

This study was originally conceived as a comparative effectiveness study using a non-inferiority approach, similar to the US study described by Mathersul et al [37, 46]. This proposed trial would have compared virtually-delivered SKY (v-SKY) to virtually-delivered cognitive processing therapy (CPT) in a non-inferiority trial, with the key innovation being virtual delivery of SKY. However, formal consultation with experts in veteran mental health care and veterans who have lived experience with PTSD indicated that the SKY intervention would likely be most useful in a Canadian context if it were to be integrated into the current treatment environment instead of being compared to a standard of care treatment. For instance, many patients in specialty clinics have not responded to existing treatments, which emphasized a need for more complementary therapeutic options. These discussions also identified wait times for access to care between 4–8 weeks, which is comparable to the wait list control time period. Likewise, as per our earlier estimates, a high number of veterans with PTSD may not be actively receiving treatment for their illness. Thus, a wait list control design was considered as the most appropriate, relevant, and feasible.

Several RCTs of SKY for veterans living with PTSD have been conducted using waitlist control designs including in the United States [29] and Australia [38]. Using a waitlist control design encompasses using a control group that is not actively receiving treatment for their illness during the intervention period. Baseline assessments will be conducted with the active intervention (ACT) and waitlist control (WLC) groups before the active intervention group receives the intervention. After the 6-week intervention period for the ACT group, there will be a 2-week data collection period for both the ACT and WLC groups. After this 2-week period, the WLC group will begin the intervention for 6-weeks and the ACT group will not. After the WLC group’s 6-week intervention, there will also be a 2-week data collection period for both groups.

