### Effectiveness

The primary outcome (PCL-5) will be measured at baseline, 6-weeks, 12-weeks and 30 weeks. The distribution of PCL-5 scores will be examined and an appropriate transformation to correct the possible non-normality will be applied if required. Repeated measures analysis of variance will be used to compare the active intervention and WLC groups at T2, T3, and T4 while adjusting for baseline measures. The demographic characteristics, including age, sex, gender, and baseline symptom severity will be compared between intervention and control groups and the comparison of the primary outcome will be adjusted for significant confounders that may be identified over the course of the study. If significant, this will be included in the repeated measures analysis of variance for adjustment. Descriptive and exploratory statistics will be used to describe and compare the exploratory outcomes (depression, anxiety, pain, and quality of life) between intervention and control groups [58]. This will be an intention-to-treat analysis, where all participants who are randomized will be included in the analysis. There are no pre-planned subgroup analyses.

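### A participant judged unsafe to continue SKY is removed from the study rather than only from the sessions, which may leave informative missing data at week 6 in the active arm alone

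*Protocol article*

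**What the plan says.** Risks and safety describes what happens when someone has adverse effects during SKY. The decision starts with the instructors: "Instructors will consult with study staff to determine if participants experiencing such adverse effects should be permitted to continue". The consequence is then stated: "If considered medically unsafe to continue, the participant will be removed from the study". The participant is also advised to see a primary care provider or an emergency department.

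Data management and confidentiality covers early withdrawal in a paragraph on voluntary participation: "If participants withdraw from the study early, any information that was collected will still be used for the study unless they request otherwise". It then adds: "No new information will be collected from them".

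On timing, the Trial design section has a 2-week data collection period after the active arm's six weeks, and continues: "After this 2-week period, the WLC group will begin the intervention for 6-weeks and the ACT group will not". Table 4 sets the primary outcome as the change in PCL-5 from baseline to six weeks (T2).

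On the analysis, the Effectiveness section under Data analysis states: "This will be an intention-to-treat analysis, where all participants who are randomized will be included in the analysis".

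On how often the rule might be used, Risks and safety reports that in previous investigations "SKY is well tolerated among participants with no reported adverse events". It lists only mild theoretical effects: anxiety, boredom and detachment.

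**The concern.** What becomes unsafe is the SKY session, but what ends under the stated rule is study participation. Filling in an online questionnaire is a separate matter from attending a breathing session, and the rule does not separate them.

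Two features make this more than loose wording. First, before T2 only active-arm participants attend sessions, so a removal triggered by SKY has no counterpart in the waitlist arm. Second, the loss is plausibly related to outcome. Anxiety and detachment lie close to what the PCL-5 measures, and participants are encouraged to practise in situations they have been avoiding. People removed for such effects may well differ at week 6 from those who continue.

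At stake is the primary comparison, because an analysis plan can only make assumptions about T2 scores that were never collected. If the assessments do stop, PHQ-9 item 9, which the trial uses to check for suicidal ideation at each assessment, would also stop in a group whose safety data matter.

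**Working it through.** **The plan's own figure.** The only numerical yardstick is in the Sample size justification: difference 5, SD 11, 80% power, 5% type I error (taken as two-sided), 76 per group.

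n per group = 2 × (1.96 + 0.8416)² × 11² / 5² = 2 × 7.849 × 121 / 25 = 75.98, rounded up to 76.

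The figure reproduces. With 25% dropout, 76 / 0.75 = 101.3, or 102 per group, against 100 stated. That gap is trivial and is not part of this point. The 5-point difference is used below as the scale for the bias.

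**Who can be removed before T2.**
- Active arm: sessions run in weeks 1 to 6, before T2, so the rule can apply.
- Waitlist arm: sessions start after the T2 data collection (Trial design; Table 1 also places them after T2), so a removal triggered by SKY cannot occur before T2.

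**Bias formula.** Let p be the share of the active arm removed before T2. Let D be the number of PCL-5 points by which those removed would have fared worse than those retained. If the mean improvement among the retained is m, the mean for the whole randomised arm is (1 − p) × m + p × (m − D) = m − pD. An analysis resting on the observed T2 values estimates m. The bias is therefore m − (m − pD) = pD, in favour of SKY when D is positive.

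**Values.** The article gives neither p nor D, so both are assumed. D = 11 is one planning SD; D = 20 is a high value. The type I error column takes a true intention-to-treat difference of zero, SD 11 and about 75 analysed per arm, so the standard error is 11 × √(2/75) = 1.80.

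| p | D | Bias = pD | Share of planned 5 points | Two-sided type I error |
|---|---|---|---|---|
| 1% | 11 | 0.11 | 2% | 0.050 |
| 2% | 11 | 0.22 | 4% | 0.052 |
| 5% | 11 | 0.55 | 11% | 0.061 |
| 5% | 20 | 1.0 | 20% | 0.086 |
| 10% | 20 | 2.0 | 40% | 0.20 |

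The first two rows fit best with the article's report of no adverse events in earlier SKY studies. The last two need removal rates or outcome differences that nothing in the article suggests. If those removed gave T2 data, this source of bias would be zero in every row.

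**The case against.** The strongest reply is that four stronger readings go beyond the text. Each is largely right.

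- **That the plan stops data collection after a safety removal.** It does not say so. The sentence on collecting nothing new belongs to voluntary withdrawal, and Risks and safety is silent on later assessments. The loss is an inference from the words of the removal rule. It is still the natural one, because nothing in the article keeps removed participants in the T2 to T4 schedule.
- **That the plan treats every stop of SKY as leaving the study.** It does not. The implementation evaluation interviews participants who have passed T3, and includes people who dropped out of the intervention. Ordinary non-completers are thus expected to reach T3. The problem is confined to those judged medically unsafe to continue. The interviews do not fill the gap: they cover at most 16 participants, take place after T3 and supply no week-6 PCL-5.
- **That the rule flatly contradicts intention to treat.** Including everyone randomised does not promise that every T2 value is observed, and 25% dropout is already planned for. Missing-data methods may be in an analysis plan not shown, so their absence is no criticism. The rule works against the promise without making it impossible to keep.
- **That the comparison is biased towards SKY, perhaps by a quarter.** One can construct this: if 10% are removed and worsen by 5 points while the rest improve by 5, the true effect is 0.90 × 5 + 0.10 × (−5) = 4.0 against an estimate of 5.0, a ratio of 1.25. But the article expects few, mild effects, and an acute medical problem during a session need not be caused by SKY or linked to PTSD severity. The direction is likely but not established.

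What remains is that the article states this rule; it is not a detail left to another document. The rule as written risks losing outcomes that no later analysis can recover.

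**Conclusion.** The point holds in limited form. The removal rule takes participants out of the study, not only out of the sessions, and before the primary endpoint it can act only in the active arm. It may therefore cause informative missing data in one arm at T2, and it fits poorly with the intention-to-treat statement.

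A bias towards SKY rests on three assumptions: that removal ends assessment, that those removed would have done worse on the PCL-5 than those retained, and that the analysis does not adequately handle the missing values. On the article's own expectation of very few adverse effects, the bias is close to zero, and it reaches about a tenth of the planned difference only if some 5% of the active arm is removed with an 11-point difference. This is a modest threat to the result. It merits correction because the remedy is nearly free and must be in place before the data are lost.

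**What to change.** Reconcile Risks and safety, Data management and confidentiality, and the Effectiveness section so that ending SKY sessions and leaving the study are separate events. State that a participant whose sessions are stopped stays scheduled for the T2, T3 and T4 questionnaires unless they withdraw consent to follow-up, and that the reason and date are recorded for each event. Limit the sentence on collecting no new information to those who withdraw that consent. The clinical decision on whether sessions stop is untouched.

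The cost is a change of wording in the protocol and consent form, with ethics board approval of the amendment, and a few extra online questionnaires on a system already in use. If removals are as rare as expected, the extra work is negligible.
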